### Covariate adjustment

If we have enough statistical power, analyses to compare interpersonal art psychotherapy and UC usual care will include the relevant baseline outcome measures.

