**Methods:**

A multicentre, two-arm, parallel-group, single blind individually randomised controlled trial with 150 adults within NHS secure care who have borderline to mild/moderate intellectual disability. The primary outcome is the frequency/severity of aggressive behaviour, measured on the Modified Overt Aggression Scale (MOAS) 19 weeks post-randomisation, analysed using a linear mixed-effect model, adjusted for baseline MOAS and stratification by gender and psychosis diagnosis. Changes in aggressive behaviour will be evaluated using weekly MOAS scores between 19 and 38 weeks. Patient distress relating to psychiatric symptoms will be assessed using the Brief Symptom Inventory Positive Symptom Distress Index across baseline, 19, and 38 weeks. Health-related quality-of-life will be assessed using self- and proxy-reported EQ-5D three-level (EQ-5D-3L) and Recovering Quality of Life 10-item measures, the latter to estimate the ReQoL Utility Index, across baseline, 19, and 38 weeks. The self-reported EQ-5D-3L is collected using an adapted version for people with intellectual disabilities. Resource-use is collected based on secure care records, to estimate intervention and healthcare costs over 19 and 38 weeks. HRQoL and cost data will inform cost-effectiveness based on the incremental cost per quality-adjusted life year over 38 weeks.

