### Sample size

The primary objective is to assess the effectiveness of art psychotherapy in reducing the frequency and severity of aggressive behavior in adult secure care as measured by the Modified Overt Aggression Scale (MOAS) [16]. Based on the results of the feasibility study [11], we assumed a minimum clinically important difference (MCID) of 5 points on the MOAS scale, a common standard deviation of 10 points in the control and intervention groups, and a correlation of 0.25 between the baseline and post-treatment MOAS scores. In addition, we may need to account for clustering by therapist, as a single therapist will apply the intervention to more than one patient. We assumed that each site would have a minimum of 2 therapists and the intraclass correlation (ICC) of the MOAS scores for the same therapist would be 1% in the intervention arm. Under these assumptions, 80% power and a type I error rate of 5%, 59 participants would be required in each arm. To account for an assumed attrition rate of 20%, this figure is inflated to a final sample size of 75 participants per arm, yielding a final sample size of 150 participants.

This would also allow the study to detect a change of 0.5 points on the Brief Symptom Inventory (BSI) Positive Symptom Distress Index (PSDI), used to evaluate changes in patient distress related to psychiatric symptoms [17]. Using an estimated SD of 0.8, the sample size calculated above would result in a power greater than 90% for the BSI comparison.

If the target recruitment (sample size) is not achieved, we will use sensitivity analysis with appropriate statistical methods as planned in the statistical analysis section. If the effect size (i.e. the mean difference of change in MOAS and its standard deviation) differs from our assumptions used in the sample size calculation, this may affect the power/sample size as shown in Table 1.

**Table 1 Tab1:** Potential effects of differing effect sizes and standard deviations on the sample size

Effect size	Power	SD	Method	Correlation (baseline and follow-up)	Alpha	Sample size (per arm)	Final sample size (inc. 20% dropout)
4	0.8	10	ANCOVA	0.25	0.05	92	230
6	0.8	10	ANCOVA	0.25	0.05	41	103
5	0.8	8	ANCOVA	0.25	0.05	37	93
5	0.8	12	ANCOVA	0.25	0.05	85	213

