### Primary outcome

The primary outcome is the frequency and severity of aggressive incidents as measured by the Modified Overt Aggression Scale (MOAS) at week 19 post-randomisation.

The MOAS is completed by a research nurse or clinical support officer at baseline (prior to randomisation), and weekly from week 19 to week 38 post-randomisation, and if necessary, checking with a member of the ward team to ensure that it accurately reflects the participant’s behaviour. The MOAS is not always completed by the same research nurse/clinical support officer, so we are recording who has conducted each assessment.

The MOAS is a validated observer-rated measure that assesses the frequency and severity of aggressive incidents among people with ID over the past week (ICC = 0.93 [16]). The scale consists of four categories: verbal aggression, aggression against property, auto-aggression (against self), and physical aggression (against others). Each category will be scored using a 5-point scale (0 = no events within that category, 4 = most severe form of aggression within the category). The rater selects as many items as are appropriate. The items in each category are summed. The summed scores are multiplied by the severity weight for that category (verbal aggression × 1, aggression against property × 2, auto-aggression × 3, physical aggression × 4). The weighted scores are summed to obtain the total MOAS score, with a higher score indicating more aggressive behavior [16]. Thus, the primary outcome is a change in the MOAS score from baseline to week 19 post-randomisation.

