### Analysis of primary outcome

The aim of the primary analysis is to examine the effectiveness of art psychotherapy in reducing the frequency and severity of aggressive incidences compared to usual care, as measured by the change in MOAS score from baseline to week 19 post-randomisation. The distribution of the MOAS scores will be assessed graphically using histograms and the mean (SD) or median [IQR] of the change in score from baseline to week 19 will be tabulated overall and by trial arm (art psychotherapy versus usual care). The change of primary outcome from baseline to week 19 will be assessed graphically using a scatter plot.

The primary outcome analysis will be performed on an ITT basis. Initially, we will use a linear mixed-effect regression model [27, 28], with the week-19 MOAS score as the dependent variable and the randomisation group as the independent variable, adjusted for the baseline MOAS score, random effect of the variable indexing strata based on gender and diagnosis of psychosis. In addition, we anticipate potential clustering in the intervention arm due to therapists. We will examine this by the ICC from the linear mixed-effect model and if there is a considerable amount of heterogeneity in the primary outcome associated with therapists, we will adjust the effect estimate for the partial clustering due to therapists. For this, both partially homoscedastic and heteroscedastic regression models will be explored, and we will report the results as appropriate. The homoscedastic model assumes between-cluster variability is only present in the intervention arm and the individual level variation is the same in both arms. The heteroscedastic model assumes between-cluster variability is only present in the intervention arm but allows different individual level variation in intervention and control arms [29, 30]. From the initial model(s), we will present the estimated difference in MOAS score at week-19 for the intervention group compared to the control group with 95% CI.

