### Analysis of secondary outcomes

Secondary outcomes include the cost-effectiveness of art psychotherapy (EQ-5D-3L and ReQoL-UI), longitudinal changes in aggressive behavior (weekly MOAS score) and changes in patient distress relating to psychiatric symptoms (BSI PSDI). The distribution of the secondary outcomes will be assessed graphically using histograms and boxplots. Depending on the score distributions, the mean (SD) or median [IQR] will be tabulated overall and by trial arm (art psychotherapy versus usual care).

For the longitudinal changes in aggressive behavior using the weekly MOAS score from week 19 to week 38, the changes will be graphically explored by plotting the mean weekly MOAS scores. As an exploratory analysis, a repeated measures ANCOVA model will be fitted which will include treatment group and the baseline value as the independent variables, and with the weekly MOAS score as the dependent variable. Analyses will be adjusted for stratification based on sex and diagnosis of psychosis.

Further secondary outcomes analyses will be performed as ITT analyses. The secondary outcomes of EQ-5D-3L, ReQoL-10 and BSI PDSI will be recorded at three time points (baseline, 19 and 38 weeks post randomisation). We will use separate linear mixed-effect models with week 19 and 38 scores (EQ-5D-3L, ReQoL-10 and BSI PDSI) as the dependent variables and the interaction of randomisation group with time (week 19, week 38) as the independent variable, adjusted for relevant baseline scores, random effect of the variable indexing strata based on gender and diagnosis of psychosis, and a random effect of clustering (by therapist). We will present the estimated difference in EQ-5D-3L/ReQoL-10/BSI PDSI scores at week 19 and 38 for the intervention group compared to the control group with 95% CI.

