The study has found it harder to recruit participants than anticipated and has led to a slower recruitment rate. An 80% power was approved by the NIHR and resulted in a reduction in the required sample size. However, it is anticipated that the study may not achieve the current target sample size of 75 participants per arm. Due to the smaller sample size, we could have wider confidence intervals, reflecting greater uncertainty about the true effect size; as such, results may need to be interpreted with this in mind. However, we have planned to use bootstrap techniques to compute the bootstrap confidence intervals for the effect estimates and report them.

For the economic analysis, the primary HRQoL measure for estimating QALYs is the self-reported, adapted EQ-5D-3L. The rationale is that the self-reported, adapted EQ-5D-3L best aligns with the current NICE methods for technology appraisal guidelines and has been developed specifically for people with learning disabilities. However, there are complications within this patient population that might mean that although NICE prefers the EQ-5D-3L and the adapted version has face validity in the patient population (i.e. those with learning disabilities), it might not be the most appropriate measure to use for the economic analysis; therefore, psychometric analyses are proposed to inform the preferred outcome for the economic analyses. The use of psychometric analyses means the choice of outcome measure for the economic analysis will be chosen post-hoc (albeit, the psychometric analyses will be completed before conducting the economic evaluation); however, as post-hoc choices can allude to data/outcome mining (e.g. making the results fit the preferred outcome), this post-hoc choice does not change the primary outcome for the economic analyses which will remain the adapted, self-reported EQ-5D-3L. Rather, the psychometric analyses results will be published alongside the economic analyses, with the economic analyses results, discussion and conclusion informed by the psychometric analyses to suggest which outcome measure has the best psychometric performance and therefore may be the more ‘appropriate’ outcome for the economic analysis, despite the primary outcome remaining the adapted, self-reported EQ-5D-3L.

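### The Covariate adjustment section makes baseline adjustment depend on adequate power, which contradicts the stated models and the sample size and leaves open which primary model governs

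*Protocol article*

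**What the plan says.** Under Covariate adjustment, the article says: "If we have enough statistical power, analyses to compare interpersonal art psychotherapy and UC usual care will include the relevant baseline outcome measures". That sentence is the whole section.

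Elsewhere the same adjustment carries no condition:

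- The abstract describes the primary outcome as "analysed using a linear mixed-effect model, adjusted for baseline MOAS and stratification by gender and psychosis diagnosis".
- Analysis of primary outcome specifies a linear mixed-effect model "with the week-19 MOAS score as the dependent variable and the randomisation group as the independent variable, adjusted for the baseline MOAS score". It reports the estimated difference in week-19 MOAS with a 95% CI.
- Analysis of secondary outcomes has the EQ-5D-3L, ReQoL-10 and BSI models "adjusted for relevant baseline scores, random effect of the variable indexing strata based on gender and diagnosis of psychosis".

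The Sample size section assumes "a correlation of 0.25 between the baseline and post-treatment MOAS scores", and its Table 1 gives ANCOVA as the method. The Discussion adds that "it is anticipated that the study may not achieve the current target sample size of 75 participants per arm", and Sensitivity analyses also treats a lack of power as a live possibility.

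The Primary outcome section closes with: "Thus, the primary outcome is a change in the MOAS score from baseline to week 19 post-randomisation".

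**The concern.** Three things do not fit together.

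1. **Contradiction.** One section makes optional what three other places state as fixed. The article's Background says that it specifies the covariates of the adjusted analyses, so this is a matter the article sets out to settle.
2. **Reversed logic.** A baseline score that predicts the outcome removes residual variance. Low power is a reason to keep it.
3. **Conflict with the sizing.** The stated 80% power already counts on the baseline term.

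At stake is which model produces the primary estimate. With an undefined power condition and an expected shortfall, an analyst could defend either the adjusted or the unadjusted model after the achieved numbers and variance are known. The two give different estimates and p-values, which undercuts the article's stated aim of limiting data-driven results.

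**Working it through.** **Inputs from the article.** Difference δ = 5, SD σ = 10 in both arms, baseline/follow-up correlation r = 0.25, power 80%, type I error 5% (Sample size); two-sided, taken from the 2-sided 95% CI in Statistical principles; 1:1 allocation (Randomisation). With 75 per arm and 20% attrition, 75 × 0.8 = 60 are analysed per arm.

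**Step 1: reproduce the plan's figure.** For ANCOVA, n per arm = 2(z₀.₉₇₅ + z₀.₈₀)² σ²(1 − r²)/δ².

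- (1.96 + 0.8416)² = 7.849
- 1 − 0.25² = 0.9375
- n = 2 × 7.849 × 100 × 0.9375/25 = 58.87, rounded up to **59**, as stated

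Inflated for attrition, 59/0.8 = 73.75, so 74 against the stated 75, which is close enough.

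**Step 2: the same inputs without the baseline.** n = 2 × 7.849 × 100/25 = 62.79, rounded up to **63**. So the 59 presupposes the baseline term.

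**Step 3: power with and without the baseline, comparing week-19 scores.** Noncentral t with noncentrality δ/(s√(2/n)). Adjusted: s = 10√0.9375 = 9.68, df = 2n − 3. Unadjusted: s = 10, df = 2n − 2. The article gives no size for the shortfall, so the rows below 60 are assumptions that show a range.

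| Analysed per arm | Baseline adjusted | Unadjusted week-19 |
|---|---|---|
| 60 (plan) | 80.1% | 77.5% |
| 50 (assumed) | 72.5% | 69.7% |
| 40 (assumed) | 62.6% | 59.8% |
| 30 (assumed) | 50.3% | 47.8% |

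The adjustment gains about 2.5 to 2.8 points at every size shown.

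**Step 4: what the adjustment can cost.** If the baseline were useless (r = 0), the lost degree of freedom would cost about 0.01 to 0.02 percentage points for 30 to 60 per arm. If r were 0.5 (an assumption), the gain would be about 10 to 12 points. At none of these sizes does low power argue for leaving the baseline out.

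**Step 5: hypothetical worst case.** If the baseline covariate were dropped and the change score compared instead, the variance factor would be 2(1 − r) = 1.5. Then n = 62.79 × 1.5 = 94.19, rounded up to 95 per arm, and power with 60 per arm would be about 60%. The article does not specify this model.

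**The case against.** **The baseline would not necessarily be dropped.** A reader might infer that the plan drops the baseline once recruitment falls short. No section says so. The responses to low power that the article names are bootstrap confidence intervals (Sensitivity analyses, Discussion) and sensitivity analyses (Sample size). The specific primary and secondary models keep the baseline, and one general sentence stands against them. This objection stands: the text permits the omission and does not require it.

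**The change-score loss is not the plan's.** A reader might also infer a fall to about 60% power, because the Primary outcome section and the opening aim of Analysis of primary outcome both speak of a change in MOAS. But the model takes the week-19 score as dependent variable and reports the week-19 difference; change is otherwise used for tabulation and a scatter plot. Taking the baseline out of that model leaves an unadjusted week-19 comparison. This also stands, so the change-score figure is only a hypothetical worst case.

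**The power loss is small.** About 2.5 points is minor beside Table 1, where modest shifts in effect or SD move the requirement between 37 and 92 per arm. True, and the case for a fix therefore does not rest on power alone.

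**The sentence may mean additional baseline measures.** The plural could refer to several of the measures listed under Baseline characteristics, for which a small sample is a more ordinary worry. This reading is possible but weaker: the sentence names the relevant baseline outcome measures, close to the wording used in Analysis of secondary outcomes for the matching baseline. If additional measures were meant, the sentence still needs rewriting.

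**Blinding.** The trial statistician is blind to allocation, which lowers the risk of a selective choice but does not say which model governs.

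**Conclusion.** The concern holds as an unresolved contradiction about the primary model, resting on a condition whose logic is reversed. It should be fixed; it is not a fatal flaw. On the article's assumptions (δ = 5, SD 10, r = 0.25, two-sided 5%), leaving out the baseline raises the requirement from 59 to 63 per arm and lowers power from 80.1% to 77.5% with 60 analysed per arm. The loss stays at 2.5 to 2.8 points under assumed shortfalls to 50, 40 or 30, and would be larger if the true correlation exceeded 0.25. These figures ignore therapist clustering, as does the formula that reproduces the 59.

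The documents support neither a certain loss of the baseline term nor a change-score primary analysis. They do support the finding that two primary models are permitted, with no stated rule for choosing between them.

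**What to change.** 1. Delete the power condition in Covariate adjustment. State that baseline MOAS is always in the primary model, and the matching baseline score always in each secondary outcome model, whatever sample size is achieved.
2. If the sentence was meant to cover additional baseline covariates, name them and place them in a sensitivity analysis, separate from the matching baseline.
3. Align the closing sentence of Primary outcome, and the opening aim of Analysis of primary outcome, with the model already specified: the reported effect is the baseline-adjusted difference in week-19 MOAS, and change scores are descriptive only.

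The cost is wording. No new data, visits or participants are needed, and the change restores the analysis on which the trial was sized. It should be made and dated before database lock and unblinding; if that point has passed, the article's commitment to report and justify deviations in the final report applies.

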### Assumption checking

Before the analyses, the distributions of the primary outcome (MOAS score) and secondary outcomes (EQ-5D-3L, ReQoL-10, weekly MOAS score and BSI PDSI) will be examined using histograms, QQ plots, boxplots and the Shapiro–Wilk test, to ensure they meet the distributional assumptions of mixed-effect linear regression models/ANCOVAs.

### Alternative methods if distributional assumptions not met

If the data does not meet the distributional assumptions of linear mixed-effects regression, the data will be transformed if possible (e.g. log with base 10). If transformations do not improve the distributions of scores, non-parametric/semi-parametric statistical methods or dichotomising the outcome scores will be considered. Non-parametric methods include generalised estimating equations (GEE) [31–33], quantile regression [34], and bootstrapping [35]. If a dichotomous/categorical version of an outcome is used, mixed-effect logistic [36] or multinomial logistic regression [37] will be considered.

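### The normality check is applied to raw MOAS scores and leads to an open list of fallbacks, so the primary effect measure depends on the data and may leave the 5-point scale

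*Protocol article*

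**What the plan says.** All references are to the protocol article, which describes itself as the detailed statistical and health economic analysis plan.

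- **Analysis of primary outcome.** A linear mixed-effect model of week-19 MOAS, adjusted for baseline MOAS, is fitted "initially" in the sense that later steps may follow. The difference in MOAS score with its 95% CI will be presented from the initial model or models.
- **Assumption checking.** Before the analyses, the outcome scores are examined with histograms, QQ plots, boxplots and Shapiro–Wilk, "to ensure they meet the distributional assumptions of mixed-effect linear regression models/ANCOVAs". No failure threshold is given.
- **Alternative methods if distributional assumptions not met.** On failure, "the data will be transformed if possible (e.g. log with base 10"). Then: "If transformations do not improve the distributions of scores, non-parametric/semi-parametric statistical methods or dichotomising the outcome scores will be considered". The section lists GEE, quantile regression and bootstrapping, and logistic or multinomial models for a categorised outcome. It gives no order, cut-point or rule for zero scores, and does not say whether a fallback replaces the initial model as primary.
- **Primary outcome.** The MOAS covers the past week. Each category starts at "0 = no events within that category", so a total of 0 is possible.
- **Sample size.** "we assumed a minimum clinically important difference (MCID) of 5 points on the MOAS scale", with "a common standard deviation of 10 points in the control and intervention groups".
- **Analysis population.** All randomised participants are to be analysed.

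**The concern.** The check is on the wrong quantity. A linear mixed model makes its normality assumption about residuals and random effects. The raw score can be skewed while the model remains adequate, and the comparison of means is fairly robust to skew at this sample size. A check that a zero-bounded weekly score will very probably fail therefore starts a sequence of changes that may not be needed.

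The sequence is also not fixed. The first step names a transformation that cannot take a zero, although zero is the best possible outcome. Eligibility (Inclusion criteria) accepts a historic HONOS item 1 score, so incident-free weeks are to be expected. The second step ranges from methods that keep MOAS points to a dichotomy, with nothing to choose between them except the observed data. At stake is which effect measure answers the primary question, and whether it can be set against the 5-point difference.

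**Working it through.** **1. The plan's own figure.** Inputs from Sample size: difference 5, SD 10, "a correlation of 0.25 between the baseline and post-treatment MOAS scores", 80% power, 5% type I error (two-sided, from Statistical principles).

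n per arm = 2 × [10 × (1.960 + 0.842) / 5]² × (1 − 0.25²) = 62.79 × 0.9375 = 58.87, so 59. The stated 59 is reproduced. It applies only to a mean difference in MOAS points.

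**2. Will the check fail?** The documents give no MOAS mean or zero share, so the mean was ranged. Non-negative integer scores with target SD 10 were simulated in three shapes: negative binomial, rounded gamma, and normal cut off at 0. Shapiro–Wilk was applied at the 5% level to the pooled raw scores. At total N = 118 (2 × 59) it rejected as follows:

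| Assumed mean | Negative binomial | Gamma | Cut-off normal |
|---|---|---|---|
| 3 to 10 | 100% | 100% | 100% |
| 15 | 100% | 100% | 83% |
| 20 | 96% | 99% | 11% |
| 30 | 64% | 75% | 5% |

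At N = 80 and N = 150, rejection was at least 99.7% for every mean up to 10. The check usually passes only when the mean is well above 15 and the shape is close to normal.

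**3. Is the linear comparison unsafe in such data?** With negative binomial scores, equal arms and 59 per arm, the type I error of a plain t-test was 3.6%, 4.6%, 5.3%, 5.1% and 5.0% at means 3, 5, 8, 10 and 15. The nominal level is 5%. The check would thus set aside an analysis whose error rate is sound.

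**4. What log10 does to zeros.** For a negative binomial with mean m and variance 100, P(0) = (m/100)^[m²/(100 − m)].

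- m = 5: 0.05^(25/95) = 0.455
- m = 8: 0.08^(64/92) = 0.173
- m = 10: 0.10^(100/90) = 0.077
- m = 15: 0.15^(225/85) = 0.007

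With a true 5-point benefit at means 10 v 5, log10 without an offset excludes 7.7% of controls and 45.5% of the intervention arm. The exclusion depends on the outcome and is unequal between arms. Power on the remaining positive scores was about 41%, against 77% for the raw comparison. At means 15 v 10 the same analysis had more power than the raw one (87% v 76%), so the firm objection is to the selection of participants; the power result depends on the assumed means.

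**5. Does an offset solve it?** Log10(y + 1) keeps everyone, but at N = 118 it still failed Shapiro–Wilk in 71–100% of trials at means up to 10. The plan would then move to its second, open step.

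**6. Scale.** A difference in log10 scores is a ratio, and a logistic coefficient is a log odds ratio. Neither converts to 5 MOAS points. An identity-link GEE and a bootstrap of the mean difference do stay in points. Quantile regression gives points at a quantile, which is a different quantity from the mean difference that sized the trial.

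**The case against.** Three stronger readings are tempting, and the documents do not support them.

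*The linear model will almost certainly be displaced.* The plan does not say so. Analysis of primary outcome still promises the MOAS difference from the initial model or models, Shapiro–Wilk is one of four checks, and no p-value triggers the switch. In a near-normal shape with a mean of 20 or more the check would usually pass. What stands is an ambiguity over which result is primary.

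*Incident-free participants will be dropped.* Log10 is only an example, qualified by "if possible" in substance, and the intention-to-treat statement points the other way. A full plan could also hold an offset. The exclusion follows only if log10 is used without one.

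*Dichotomising loses power.* This holds for a normal outcome. A midpoint cut turns 5 points with SD 10 into 59.9% v 40.1%, which has about 57% power at 59 per arm without baseline adjustment. It does not hold for skewed scores. With negative binomial scores and a 5-point benefit, a median split had 81–100% power against 76–78% for the raw t-test. Loss of power is therefore not part of this point.

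It is also fair to say that the plan was approved before database lock and that the trial statistician is blind to allocation. That limits choice by result, but it does not settle what is being estimated. The list of alternatives includes methods that keep the points scale, and bootstrapping is already among them. The plan simply does not prefer them.

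**Conclusion.** The point holds in a limited form and should be fixed. The check is on raw scores when it should be on residuals. With the planned SD of 10 it very probably fails unless the MOAS mean is well above about 15 and the shape is near normal. The first response named cannot handle zeros as written, the later choice is open, and the plan does not say whether the estimate in MOAS points remains primary. The primary effect measure is thus left to depend on the observed distribution, and some of the options cannot be set against the 5-point difference.

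The rejection rates, zero shares and power figures rest on assumed means and shapes. The mismatch between raw scores and residuals, the undefined log of zero and the missing statement of which result is primary rest on the text alone.

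**What to change.** 1. State that the baseline-adjusted mean difference in week-19 MOAS points, from the model in Analysis of primary outcome, is the primary estimate whatever the distribution.
2. Replace Shapiro–Wilk on raw scores with inspection of the fitted model's residuals.
3. If residuals are skewed or heteroscedastic, keep that estimate and report a robust or bootstrap confidence interval.
4. Label any transformed, log-link or dichotomised analysis as supportive, and use only methods that retain zero scores.

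The cost is a change of wording, with no extra data or participants. The drawback is that when scores are very skewed the raw-scale comparison may have less power than some alternatives. In the simulations it had 76–78%, against 96–100% for log10(y + 1). That is the price of an estimate that can be read against 5 points, and the supportive analyses can show the rest.
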